### Blinding

Assessment interviews will be conducted and analyzed by clinician-raters blinded to the treatment condition. Raters at post and follow-up assessments must not be the therapist of the particular patient being assessed and analyzed.

### Statistical Methods

Our primary efficacy analysis will be based on the full analysis set (FAS) according to the intention-to-treat (ITT) principle, reflecting the recommendations given in relevant guidelines (67). The FAS is defined to include all patients enrolled who are assigned to the treatment group they were originally randomized to, regardless of whether they actually underwent the assigned treatment or not. This will be the primary population for evaluating all efficacy endpoints and subject characteristics. Additionally, the per-protocol (PP) population, including all FAS patients with no major protocol deviations, will serve as a secondary analysis population and be used for sensitivity analyses. Before lock of the database, each patient's allocation to the FAS or PP population will be defined in the statistical analysis plan.

The two hypotheses to be assessed in the primary efficacy analysis are ordered hierarchically: In the first step, the null hypothesis ${\text{H}}_{0}^{\text{I}}$: $\mu_{\text{CBT}+\text{PPP}}^{\text{T}3-\text{T}2}$ = $\mu_{\text{CBT}}^{\text{T}3-\text{T}2}$ for the primary outcome “change in teacher CBCL (Teacher Report Form/TRF) score between T2 and T3” is tested at the two-sided significance level of 5% against the alternative ${\text{H}}_{1}^{\text{I}}$: $\mu_{\text{CBT}+\text{PPP}}^{\text{T}3-\text{T}2}$ ≠ $\mu_{\text{CBT}}^{\text{T}3-\text{T}2}$. If ${\text{H}}_{0}^{\text{I}}$ can be rejected, the null hypothesis ${\text{H}}_{0}^{\text{II}}$: $\mu_{\text{CBT}+\text{PPP}}^{\text{T}4-\text{T}2}$ = $\mu_{\text{CBT}}^{\text{T}4-\text{T}2}$ for the second primary endpoint “change in TRF score between T2 and T4” is tested at the two-sided level of 5% against its alternative ${\text{H}}_{1}^{\text{II}}$: $\mu_{\text{CBT}+\text{PPP}}^{\text{T}4-\text{T}2}$ ≠ $\mu_{\text{CBT}}^{\text{T}4-\text{T}2}$. Application of this multiple test procedure for a priori ordered hypotheses ensures control of the family-wise type I error rate at a level of 5%. The null hypotheses will be assessed using a linear mixed multi-level model with patients at level 1 and children at level 2, adjusting for center, number of comorbidities, number of children, baseline TRF score at T2, and length of waiting period between T1 and T2 (in weeks).

Data missing for the primary outcome variable will be replaced by using multiple imputation (68) which takes the covariates treatment group, center, number of comorbidities, number of children, baseline TRF score at T2, and length of waiting period between T1 and T2 (in weeks) into account by applying the fully conditional specification method (69). This will be realized using the option “FCS” of the SAS “MI” procedure implemented in SAS 9.4. Sensitivity analyses will be performed by applying alternative methods dealing with missing data such as complete case analysis. All secondary outcomes will be evaluated descriptively, and descriptive *p*-values are reported together with 95% confidence intervals for the corresponding effects. Further exploratory analyses will be performed to identify potential prognostic factors (e.g., parental disorder, child psychopathology, socio-economic status) and mediators (e.g., Brief Symptom Inventory/BSI, Parenting Questionnaire/EFB, Parental Stress Inventory/ESF) for an intervention effect. The safety analysis includes calculation of frequencies and rates of adverse and serious adverse events together with 95% confidence intervals. All analyses will be performed with SAS version 9.4 or higher.

The health-economic evaluation will involve a combination of a cost-effectiveness analysis (CEA) and a cost-utility analysis (CUA) (70, 71). The economic evaluation will be done from a societal perspective (all relevant costs) and a public health care perspective (only direct medical costs) within a 6 month time frame. In the CEA, the incremental cost-effectiveness ratio (ICER) will be expressed as the incremental costs per point improvement on the primary clinical outcome (CBCL scores in children; parents' BSI scores). In the CUA, the ICER will be expressed as incremental costs per quality-adjusted life year (QALY) gained as based on the EQ-5D-5L (52, 72) (parents) and KIDSCREEN-10 (63, 73) (children). Sampling uncertainty in the ICER will be handled using non-parametric bootstrapping by resampling patient-level data to generate 2,500 simulations of the ICER. We will bootstrap the SURE model (seemingly unrelated regression equations; sureg command in Stata) to allow for correlated residuals of the cost and effect equations (74). Ninety five percent confidence intervals (CI) will be obtained by the bootstrap acceptability method, since parametric techniques are inappropriate for use on skewed variables and ratios (75).The bootstrapped ICERs will be plotted in a cost-effectiveness plan where the horizontal axis reflects differences in effects and the vertical axis differences in costs. The bootstrapped ICERs will also be shown in a cost-effective acceptability curve disclosing the probability that the intervention is cost-effective for a range of willingness-to-pay ceilings (76). To test the robustness of the base-case findings, a probalistic sensitivity analysis will be done. Several assumptions made in the base-case scenario will be changed to assess their impact on the ICER (e.g., QALY calculation based on AQoL-8D).

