### Interventions

All patients will receive between 25 (short-term) and 45 (long-term) weekly or bi-weekly sessions of individual state of the art Cognitive Behavioral Therapy (CBT). A high frequency therapy with more than one session per week is also allowed. Depending on the amount and the frequency of therapy sessions, the treatment will usually last between 6 and 12 months. The number of sessions and therapy duration will be documented, thus, allowing us to include therapy duration and number of sessions as a moderating factor in the analyses.

CBT can be considered the current “treatment of choice” for mental disorders in general (32). Central elements are psychoeducation that provides a framework for psychotherapy, cognitive components (i.e., debate of dysfunctional cognitions alias Beck), as well as behavioral interventions (i.e., exposure). As all study sites are outpatient clinics for research and teaching located at university psychology departments, they commit to the highest possible state of the art standard for CBT as outlined in “proceedings in psychotherapy/Fortschritte der Psychotherapie” of which [name] (Co-PI of COMPARE-family) is an editor (33). As the study shall be conducted as naturalistic as possible and a broad range of disorders shall be included, no specific study manual has been created, rather, the respective therapy manuals of the proceedings in psychotherapy will be used in this study.

Patients randomized to the experimental group will receive 8–10 additional group or individual sessions of the Positive Parenting Program (Triple P) parallel to the last third of the psychotherapy sessions to test whether the enhancement of parenting skills will result in improved child outcome, as suggested in different studies (17, 18, 20, 27, 28), above and beyond parental CBT. Triple P is a well-established, widely used and evidence-based program to enhance parenting skills. The Triple P Kids program can be used in groups or individual sessions with parents of children aged 0–12 years (34, 35) and the Triple P Teens program in groups with parents of children aged 12–16 years (36). The Triple P elements are: (1) promotion of a positive parenting style, (2) promotion of child development, (3) dealing with problem behavior, (4) behavior training sessions (34–36).

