### Sample Size

The sample size calculation is based on the primary outcome measure (change in TRF score between T2 and T3) which is hierarchically ranked on top of the multiple testing procedure. Based on the results described above (14, 15, 64), it is assumed that the standardized treatment effect for this outcome expressed by Cohen's d amounts to d = 0.25. With a two-sided significance level of α = 0.05 and a power of 1–β = 0.8 using a two-sample *t*-test, 253 patients per group (*n* = 506 in total) are required. Since the primary outcome is measured on the child level and it is possible to enroll multiple children per patient, a hierarchical multi-level model with patients at level 1 and children at level 2 will be fitted. Taking a drop-out rate of 20 % into account, *n* = 634 patients need to be enrolled into the trial in the analysis. This attrition rate is conservative and based on results from the longitudinal STAR^*^D study that also carried out long-term follow-up assessments (13), as well as on other studies in the field that report even lower attrition rates (65, 66). The problem of attrition and missing values will also be addressed in the analysis by applying the intention-to-treat principle. For missing values, imputation techniques will be applied, thus partly resolving this problem. Since it is assumed that parts of the outcome variance can be explained by the inclusion of covariates, the actual power of the analysis by a linear multi-level model is expected to be higher than 1–β = 0.8. Assuming that the number of children enrolled per patient amounts to 1.5, we expect that *n* = 950 children will participate in the trial. The enrollment of more than one child per patient is expected to yield an additionally increased power. Sample size calculation was performed using SAS v9.4 (SAS Institute, Cary, NC).

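### The primary model and sample size make no allowance for clustering by Triple P group, which can arise in the experimental arm only, so the 5% level is not assured and the power margin is unquantified

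*Protocol article*

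**What the plan says.** The Statistical Methods section states the model in full: "The null hypotheses will be assessed using a linear mixed multi-level model with patients at level 1 and children at level 2". The adjustment covariates are center, number of comorbidities, number of children, baseline TRF score at T2 and length of the waiting period. Neither Triple P group nor therapist appears. The same section says that the ordered testing of the two primary hypotheses "ensures control of the family-wise type I error rate at a level of 5" percent.

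On delivery, the Interventions section says: "Patients randomized to the experimental group will receive 8–10 additional group or individual sessions of the Positive Parenting Program (Triple P"). The Treatment Period section repeats the choice between group and individual sessions. Interventions describes the Kids program as usable in either format and the Teens program in groups. CBT is individual in both arms.

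The Sample Size section uses a two-sample t-test on patients: "With a two-sided significance level of α = 0.05 and a power of 1–β = 0.8", with an effect that "amounts to d = 0.25", giving "253 patients per group". It adds that covariates should lift power above 0.8 and that "The enrollment of more than one child per patient is expected to yield an additionally increased power". It names no factor that would lower power other than drop-out.

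**The concern.** Patients are randomized individually, but some in one arm are then treated together. Members of a Triple P group share a trainer, a set of peers and a run of sessions, so their children's outcomes may be correlated. Control patients have no such groups. This is a partially nested design.

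The terms already in the model do not cover it. The patient-level random effect handles siblings, not unrelated families who attend the same group. Center adjustment removes differences between centers that both arms share, not clustering among experimental patients within a center.

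The first hypothesis (change from T2 to T3) is the gatekeeper for the second (T2 to T4) in a trial described as confirmatory. Ordered testing holds the family-wise level only if each component test holds its own. A standard error that is too small undermines that condition. Separately, the sample size treats patients as independent, and the discussion of power lists gains without setting this possible loss against them.

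**Working it through.** **1. The plan's own figure.** Inputs from Sample Size: d = 0.25 (SD = 1), two-sided α = 0.05, 253 per arm.

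- Standardized signal: 0.25 × √(253/2) = 2.812.
- Normal approximation: power = Φ(2.812 − 1.960) = 0.803. With the noncentral t distribution it is 0.801, and 253 is the smallest sufficient number per arm.
- "Taking a drop-out rate of 20 % into account": 253/0.8 = 316.25, rounded up to 317 per arm, so 634.

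The plan's calculation is reproduced. It contains no design effect.

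**2. Clustering in one arm.** Let m be the Triple P group size, ICC the within-group correlation, and g the share of the experimental arm treated in groups. None of the three is given in the article, so all are assumptions.

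- Design effect in the experimental arm: DE = 1 + g(m − 1)ICC
- Variance ratio for the treatment difference: VR = (1 + DE)/2
- True level of the uncorrected test: 2[1 − Φ(1.960/√VR)]
- Power with a valid standard error: Φ(2.812/√VR − 1.960)

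Example with g = 1, m = 6, ICC = 0.05: DE = 1.25, VR = 1.125, √VR = 1.061. Level = 2[1 − Φ(1.848)] = 0.065. Power = Φ(2.651 − 1.960) = 0.755.

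| g | m | ICC | VR | True level | Power |
|---|---|---|---|---|---|
| 1 | 6 | 0.01 | 1.025 | 5.3% | 79.3% |
| 1 | 4 | 0.02 | 1.030 | 5.4% | 79.1% |
| 1 | 6 | 0.05 | 1.125 | 6.5% | 75.5% |
| 1 | 8 | 0.05 | 1.175 | 7.1% | 73.7% |
| 1 | 8 | 0.10 | 1.350 | 9.2% | 67.7% |
| 0.5 | 6 | 0.05 | 1.063 | 5.7% | 77.9% |
| 0.25 | 6 | 0.05 | 1.031 | 5.4% | 79.1% |

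**3. Does the patient-level term absorb the clustering?** A simulation (10,000 trials per setting, whole arm in groups) kept a family effect, with one or two children per family, and left out the group term. The rejection rate under the null was 0.048 at ICC 0, 0.057 at m = 6 and ICC 0.02, 0.068 at m = 6 and ICC 0.05, and 0.075 at m = 8 and ICC 0.05. It does not absorb the clustering, and the formula above is, if anything, slightly mild.

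**4. Offsetting gains in power.** These are also unquantified in the article.

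- Covariates: if they explain a share R² of the variance, VR is multiplied by (1 − R²). The value that restores the original power is 1 − 1/VR: 0.11 for VR = 1.125 and 0.15 for VR = 1.175.
- Siblings: suppose half the families enroll two children (consistent with the stated 1.5 per patient), with sibling correlation ρ. Information per family is then 0.5 + 0.5 × 2/(1 + ρ), which is 1.333 for ρ = 0.2 and 1.125 for ρ = 0.6. Extra children do not reduce the group component, so at m = 6, ICC 0.05 and g = 1 the variance ratio is 1/information + 0.25/2. That gives 0.875 or 1.014, and power of about 0.85 or 0.80.

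**5. Therapists.** If therapists treated patients in one arm only, with k patients each, VR = 1 + (k − 1)ICC. For k = 5 and ICC 0.05, VR = 1.20, the level is 7.4% and power 72.8%. If therapists treat patients in both arms, their contribution largely cancels from the treatment difference. The article does not say which applies.

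**The case against.** The strongest reply is that the effect may be small and that nothing in the article shows otherwise. Triple P may be given individually, and the group share could be low. Treating the whole arm as grouped is an upper bound: Triple P runs alongside the last third of CBT, while the full analysis set keeps patients whatever treatment they received, so early dropouts never join a group. The outcome is rated by a caregiver or teacher outside the family, one per child, and the model adjusts for the T2 score. A group effect on parents must pass through parenting and child behavior before it reaches that rater. At ICC 0.01 the level barely moves. All of this stands as a limit on the size. It does not show that the ICC is zero.

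A reader might infer more than the article supports:

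- **That the 80% power is lost.** This is not shown. Baseline adjustment and additional children could recover it in the middle cases. These gains do not, however, repair a standard error that ignores the groups.
- **That the 5% statement is wrong.** It concerns multiplicity and is correct on that point, provided each component test is valid.
- **That therapist clustering also inflates the error rate.** This would need therapists nested within arm, which the article does not state.
- **That the level labels signal a wrong model.** Numbering patients as level 1 and children as level 2 departs from the usual convention, but the text makes clear that several children may belong to one patient. It is a matter of numbering.

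The analysis plan is not at hand and may settle degrees of freedom, data fields or even a group term. The model in the article is nonetheless stated with its levels and covariates, so the missing group term is a feature of the stated analysis and not merely a detail left for later.

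**Conclusion.** The point holds in conditional form. The confirmatory model and the sample size ignore clustering by Triple P group, which the design permits in one arm only. Any positive group ICC makes the treatment-effect standard error too small, so the 5% level of each test is not assured. Under the assumed range in the table (the whole arm in groups of 4 to 8, ICC 0.02 to 0.10), the inflation runs from negligible to material, and with half or less of the arm in groups it is modest. On power, the defensible conclusion is that the margin is unquantified: the article counts the gains from covariates and siblings but not this loss. The therapist question remains open until it is known whether therapists treat both arms.

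**What to change.** - Add to the primary model a random effect for Triple P group in the experimental arm only. Control patients and individually treated patients, including those who never joined a group, enter as singletons. Use Satterthwaite or Kenward-Roger degrees of freedom.
- Make sure that Triple P group and therapist identifiers are available in the analysis data.
- Add a therapist random effect at least as a sensitivity analysis, and state whether therapists treat patients in both arms.
- In Sample Size, replace the one-sided expectation of power above 0.8 with power over a range of group sizes, group shares and ICCs, set against the expected covariate and sibling gains. For scale, with the whole arm in groups of 6, ICC 0.05 and no such gains, restoring 80% power would need 2 × 253 × 1.125 ≈ 570 analyzed patients, or 712 enrolled (2 × 253 × 1.125/0.8, rounded up per arm) against the planned 634.
- State the nesting as children within patients.

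The cost is analysis-plan wording and two identifier fields if they are not already recorded. The confidence interval may be slightly wider and the stated power somewhat lower. If the group variance proves near zero, little is lost.

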#### Secondary Outcome Measures

Children's and parents dimensional severity index of a broad range of mental disorders according to the DSM-5 based clinical interview (Kinder-)DIPS (42–44) respectively the SIVA (45), parent's psychopathology according to the Brief Symptom Inventory (BSI) (46), personality traits (PID-5-BF) (47), children's psychopathology according to the CBCL-parentversion (37, 38), parenting skills (EFB) (48), parental stress (ESF) (49), children's and parents knowledge about mental disorders [semistructured interview adapted from Beardslee and Röhrle, (50)], direct medical costs and direct and indirect non-medical costs (TiC-P) (51), health-related quality of life in parents [EuroQoL/EQ-5D-5L, AQoL-8D (52, 53)], health-related quality of life in children (KIDSCREEN-10) (54, 55) (for details see Table 1).

**Table 1 T1:** List of diagnostic domains and measurements.

	**Who?**	**Where?**	**T1**	**T2**	**Intermediate**	**T3**	**T4**
Eligibility screening	Family	Local	x				
Socio-demographics	Parents	Local	x				
Structured clinical interview with the patient (DIPS)	Patient	Local	x	x		x	x
Structured clinical interview for children (Kinder-DIPS/SIVA)	Parent	Local	x	x		x	x
Brief Symptom Inventory (BSI)	Parents	Online	x	x	x (patient)	x	x
Personality traits (PID-5-BF)	Parents	Online	x	x		x	x
Child Behavior Checklist (CBCL)	Parents	Online	x	x		x	x
(Caregiver-) Teacher Report Form [(C-)TRF, caregiver/teacher version of the CBCL]	Teacher	Online	x	x		x	x
Parenting Skills (EFB)	Parents	Online	x	x		x	x
Parental Stress (ESF)	Parents	Online	x	x		x	x
Knowledge about mental disorders	Parents, children	Local	x	x		x	x
Direct and indirect costs in children and parents (adapted TiC-P)	Parents	Online	x	x		x	x
Health-related quality of life in parents (EuroQoL/EQ-5D-5L, AQoL-8D)	Parents	Online	x	x		x	x
Health-related quality of life in children (KIDSCREEN-10)	Parents, children (>8)	Online	x	x		x	x
(Serious) adverse events	Parents, children	Local		x	x (patient)	x	x
Psychopharmaka and other drugs	Parents, children	Local	x	x	x	x	x
Concomitant interventions	Parents, children	Local	x	x	x	x	x

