### Pre-assessment T1 and Assessment of Eligibility

After an initial screening of eligibility for an as early and effective as possible selection of patients and their families and a regular intake consultation with the patient in the outpatient clinic, the patients and their families (children over the age of 6 years) are invited to an informational session at the study center. During this session, the families are informed about the study procedure before signing their consent to participate in the study. For pseudonymized data collection, each participant is assigned a Screening-ID. To assess a broad range of DSM-5 based psychological disorders and comorbid ones as well as severity ratings, structured clinical interviews for patients (DIPS), and children (Kinder-DIPS parent version or SIVA) are conducted with the patient respectively a parent (for each child separately). The parent, with whom the Kinder-DIPS/SIVA is conducted, has to be the same for all children of a family at all measurement points. The in- and exclusion criteria are checked on the basis of the information collected during the screening and the diagnoses based on the clinical interviews. Feedback to diagnoses is given in a separate session. If a patient and its family fulfill all the in- and none of the exclusion criteria, the family is included in the trial and records for the eCRF are created for all the included family members. The family is invited to another session in which interviews about knowledge about mental disorders are conducted with each included family member. After this session codes are handed out with which the family members can log into REDCap at home to complete the questionnaires. Forms with REDCap-codes for the children's caregivers or teachers (one caregiver/teacher for each included child) are also handed out to the family with the request to forward them to the respective caregiver/teachers. There is no reference to the clinical trial of the COMPARE-family project on the caregiver/teacher's form; rather, the questionnaire is generally presented as part of a study at the department of psychology the UMR. After the final inclusion in the study, the randomization to one of the two treatment arms (CBT or CBT+Triple P) takes place. If needed, further probatory sessions can take place at the study centers. In a separate feedback session, the patient is informed about the treatment condition and results of the diagnostic process.

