## Discussion

We expect that in arm I (CBT), the parents will improve through treatment as will their children (2, 7, 12). Since, parenting skills of parents with a mental illness are likely impaired and enhancing such skills leads to better child outcomes (17, 18, 20, 27, 28), we expect that additional incremental effects will become apparent in arm II (CBT+Triple P). We will use the Positive Parenting Program (Triple P) in addition to CBT, as Triple P is an evidence-based, widely used, and well-established program. The positive effects of Triple P have been demonstrated in parents and children (22, 23, 78), although incremental effects above and beyond parental CBT have not been researched in conjunction with COPMI so far.

The established magnitude of this specific incremental effect will result in precise recommendations for this high-risk group that will impact clinical practice (i.e., practice parameters, treatment guidelines). As outlined above, COPMI are most likely to constitute the next generation of patients with a mental illness, and we assume that this intervention will contribute to the prevention of SMI in this specific high-risk group.

As studies so far have focused primarily on specific disorders (e.g., anxiety, depression) and have excluded comorbidities (1, 3), though comorbidities actually occur with the most patients, the COMPARE study will fill this research gap by including a broad range of mental disorders and by not excluding comorbidities. A double baseline measurement with multiple baselines depending on the usual waiting periods in the study centers (T1: 1st assessment of parents and children via clinical interviews and questionnaires; T2: 2nd assessment with the same instruments) will enable us to assess parental disorder effects on the child that can then be related to parental treatment effects (T3: after completion of 25 short-term to 45 long-term sessions of state-of-the-art CBT or CBT+TripleP) for a 6-month follow-up (T4). As there are differential parental psychotherapy effects on children depending on the parental remission status (early, late, and non-remitters), we will also assess such effects (9, 13). By including different therapy durations (short- vs. long-term therapy) we will be able to shed light on treatment duration effects.

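### Both primary models and the imputation model use only the T2 teacher score; adding the scheduled T1 score would gain some precision at little cost (low severity)

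*Protocol article*

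**What the plan says.** All references are to the protocol article.

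- **Primary models (Statistical Methods).** One linear mixed multi-level model specification serves both hypotheses (change from T2 to T3, then T2 to T4), with adjustment for center and for "number of comorbidities, number of children, baseline TRF score at T2, and length of waiting period between T1 and T2". The T2 score is the only teacher score in it.
- **Imputation (Statistical Methods).** Missing primary outcome values are filled in by fully conditional specification from the "covariates treatment group, center, number of comorbidities, number of children, baseline TRF score at T2, and length of waiting period between T1 and T2". The T1 teacher score is again absent.
- **Schedule (Table 1, Secondary Outcome Measures).** The row for the "Caregiver-) Teacher Report Form [(C-)TRF, caregiver/teacher version of the CBCL" is marked at T1, T2, T3 and T4.
- **T1 procedure (Pre-assessment T1 and Assessment of Eligibility).** Teacher forms ("one caregiver/teacher for each included child) are also handed out to the family") come before allocation in the described sequence: "After the final inclusion in the study, the randomization to one of the two treatment arms (CBT or CBT+Triple P) takes place".
- **Double baseline (Discussion).** The two pre-treatment assessments are presented as a design feature ("T2: 2nd assessment with the same instruments").
- **Power (Sample Size).** Power is expected to exceed 0.8 partly because "parts of the outcome variance can be explained by the inclusion of covariates".

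In the confirmatory analysis T1 appears only as the start of the waiting period. No section gives a reason for leaving out the T1 score.

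**The concern.** A single teacher rating mixes the child's stable level with error specific to that occasion. A second pre-treatment rating of the same construct usually helps to predict the later score, because two noisy readings locate the stable level better than one. It adds nothing only if T1 has no partial correlation with the outcome once T2 is known.

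The article counts on covariates for extra power, yet leaves a pre-treatment measure of the outcome itself out of a covariate list that it states in full. At stake is the width of the confidence intervals for the T3 and T4 contrasts.

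Imputation is affected too. The outcome is a change from T2, so a missing T2 form removes both the outcome and its main predictor. The T1 score is then the only other pre-treatment teacher rating. Some loss is plausible, since families are asked to pass the forms on to teachers.

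**Working it through.** **1. The stated sample size reproduces.** Inputs from Sample Size: d = 0.25, two-sided α = 0.05, power 0.80, two-sample t-test. By the non-central t distribution, power is 0.7998 with 252 per arm and 0.8014 with 253. So 253 per arm, 506 in total. With 20% drop-out, 253/0.8 = 316.25, rounded up to 317 per arm, or 634. This calculation contains no covariates.

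**2. Residual variance with and without T1.** Write r12, r23 and r13 for the correlations T1-T2, T2-outcome and T1-outcome, with equal variances. None is given in the article, so all values are assumptions.

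- T2 only: 1 − r23².
- T1 and T2: 1 − (r13² + r23² − 2·r12·r13·r23)/(1 − r12²).
- With all correlations equal to r, the explained share rises from r² to 2r²/(1 + r). For r = 0.5: 0.25 to 0.333, so the ratio is 0.667/0.75 = 0.889.

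Adjusting a change from T2 for T2 leaves the same residual as adjusting the later score for T2, so these ratios apply to the planned endpoint.

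| Pattern | Variance ratio | Evaluable N for the same precision (506 × ratio) |
|---|---|---|
| Equal, r = 0.4 | 0.918 | 465 |
| Equal, r = 0.5 | 0.889 | 450 |
| Equal, r = 0.6 | 0.859 | 435 |
| Equal, r = 0.7 | 0.830 | 420 |
| (r12, r13, r23) = (0.6, 0.45, 0.5) | 0.953 | 482 |
| (0.7, 0.5, 0.6) | 0.980 | 496 |
| First-order autoregressive, 0.7 | 1.000 | 506 |

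A wider set combined time decay with rating error: reliability 0.7-0.9, waits of 1-9 months (Limitations), treatment of 6-12 months (Interventions). It gave ratios of about 0.90-0.997 for T3 and 0.91-0.998 for T4.

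**3. Power on the article's own scale.** Sample Size defines d on the T2-T3 change, whose SD is σ√(2(1 − r23)). Adjustment for T2 reduces the residual SD to σ√(1 − r23²). The effective standardized effect is therefore 0.25·√(2/(1 + r23)). Adding T1 divides this by the square root of the variance ratio. With 253 per arm and clustering ignored:

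| Pattern | Effect, T2 only | Power | Effect, T1 + T2 | Power |
|---|---|---|---|---|
| r = 0.4 | 0.299 | 91.8% | 0.312 | 93.8% |
| r = 0.5 | 0.289 | 90.0% | 0.306 | 93.0% |
| r = 0.6 | 0.280 | 88.1% | 0.301 | 92.3% |
| r = 0.7 | 0.271 | 86.1% | 0.298 | 91.6% |
| (0.6, 0.45, 0.5) | 0.289 | 90.0% | 0.296 | 91.3% |
| (0.7, 0.5, 0.6) | 0.280 | 88.1% | 0.282 | 88.7% |

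The most favourable pattern in the decaying set (r23 = 0.706, ratio 0.896) gives 0.25·√(2/1.706) = 0.271, power 86.0%, rising to 0.271/√0.896 = 0.286, power 89.5%. The middle of that set gains about one point.

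**The case against.** **Nothing is wrong or contradictory as written.** Adjusting a change from T2 for the T2 value is standard. Sample Size says only that covariates should lift power above 0.8, and T2 alone can do that. The Discussion gives the double baseline its own purpose, namely to study effects of the parental disorder before treatment. All of this stands, and it is why the point is about efficiency only.

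**A reader might infer that the planned model has 80% power and that T1 would lift it to 83-87%.** Those figures result from placing d = 0.25 on the T2-adjusted residual SD. The article does not do that: its 80% belongs to an unadjusted test on the change score. On that scale T2 adjustment has already taken most of the gain.

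**A reader might also infer that T1 is the second-best predictor and that the family-level terms waste degrees of freedom.** No figure in the article ranks the predictors, and parent-rated CBCL and interview severity are collected too. Center, comorbidity and number of children reflect the randomization strata and do not compete with T1.

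**Equal correlations are the favourable case.** Many clinics have waits of 1-3 months, while treatment usually lasts 6-12 months and T4 follows six months later, so some decay with time is likely. The same teacher is not required at each visit, and a child may move from the C-TRF to the TRF. Each of these can shrink the gain. This stands.

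**The change is not entirely free.** The imputation text covers missing primary outcome values only and does not list T1. Adding T1 to the primary models alone could drop children who lack a T1 form. This stands and shapes the remedy.

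**Conclusion.** The point holds at low severity. A T1 teacher score is scheduled for every included child, on forms issued before randomization (though a teacher may return one later), and neither the confirmatory models nor the imputation model uses it. Validity is not in question.

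The gain runs from nothing to about 17% of residual variance. The upper end needs equal correlations of 0.7, and decay with rating error gives about 0-10%. In power, this is about 2-6 points under equal correlations and typically about 1 point under decay (3.5 at most in the patterns tried), from a level of about 86-92%. These figures assume equal variances, one child per patient, and d = 0.25 on the change score. The article supplies no correlation that would narrow the range.

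**What to change.** Before unblinding:

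1. Add the child's T1 (C-)TRF score as a further covariate in both primary models, entered separately from the T2 score.
2. Add the same score to the fully conditional specification imputation model, and state that missing T1 scores are imputed there, so that no child leaves the analysis for lack of a T1 form.

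The cost is one degree of freedom, imputation of missing T1 scores and a short addition to the analysis text. No new data are needed, and families and teachers have no extra burden.
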